### Data collection

The BCP-VAMOS implementation process will be monitored for 12 months. The data will be collected through electronic forms, a smartphone messaging application, observations, and semi-structured interviews with key informants involved in the implementation strategies. The interviews will be conducted by phone or in-person by an independent co-investigator who will not participate in the other stages of the study. The variables referring to BCP-VAMOS participants will be collected by the health professionals responsible for implementation at the baseline and during post-intervention. This information will be recorded and shared with the research team using electronic spreadsheets. A trained researcher will collect accelerometry data *in loco*. The instruments for collecting data in each stage of the study will be developed based on recent recommendations for pragmatic studies (28), the RE-AIM checklist (37), the CFIR matrices (www.cfirguide.org), and the questionnaire for effectiveness evaluation, designed for the BCP-VAMOS (33). Participants' consent will be collected by health professionals before the intervention starts. We will train independent research to evaluate the process. All data regarding the implementation of BCP-VAMOS will be managed by one single researcher to maintain data quality and reliability. The confidentiality of the participant is guaranteed using identification code numbers to match the treatment data in the computer files for each group.

### Data analysis

Quantitative data will be expressed through descriptive analysis (absolute and relative frequency, mean and standard deviation) and inferential analysis to compare the impact of the intervention between the groups. To compare the characteristics between the groups, Fischer's exact and chi-square tests will be used. To verify the effect of the intervention, Student's paired t test or Wilcoxon test (continuous variables) and McNemar test (categorical variables) will be used. To compare changes between groups, Student's t test or Mann-Whitney *U*-test will be applied. The analyses will be performed using a 5% probability, and will be generated using the Statistical Package for the Social Sciences (SPSS)^®^ software, version 22.0. Qualitative data will be fully transcribed by a researcher, and their quality will be assessed by a second researcher. Through the technique of descriptive content analysis (38), the texts will be pre-analyzed (each interview will be read), coded (reduced to units of meaning consistent with the purpose of the study), and categorized (the participants' answers will be organized). The information will be coded deductively, following the conceptual model of the study and, if necessary, inductive codes will be added until saturation is achieved (39). The data will be double-coded in the QSR NVivo^®^ 12.0 software by two trained researchers. Intercoder reliability will be assessed employing Cohen's kappa (criterion> 0.80).

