**Methods and analysis:**

A pragmatic randomized controlled trial (PRCT) of two arms comparing a group of PHC professionals who will participate in a traditional didactic approach (control group) vs. a group that will receive ongoing support (intervention group) for the implementation of BCP-VAMOS. The intervention will be available to adults (≥18 years old) registered at PHC. Program recipient's will be assessed at baseline and post-intervention (9 months after) to measure markers of physical activity and eating behavior (primary outcomes). Program's implementation process will be monitored for 12 months and will be evaluated using the RE-AIM and Consolidated Framework for Implementation Research (CFIR) frameworks.

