**Figure 3 F3:**
[figure not shown]
Online training learning modules for implementation of BCP-VAMOS, version 3.0. Brazil. Adapted from Konrad et al. (21).

**Table 1 T1:** Description of strategies for groups with and without ongoing support for the implementation of BCP-VAMOS, version 3.0. Brazil.

**Intervention stage**	**Traditional didactic approach group^a^**	**Consultee-centered training + action planning approach group^b^**
**Program dissemination, participants enrollment**	Printed material to publicize and recruit the community: posters, flyers, and business cards.	Printed material plus guidelines to optimize dissemination and recruitment: who, where, when, and how.
**Program sections** (18 sections)	T-shirt with program logo for the provider. Digital guidelines, printed material to conduct the sections, record the frequency, and monitor and evaluate the sections.	T-shirt, manual, printed material plus guidelines for each of the sections: preparation of the site, reception, content guiding, participation registration, and individual section monitoring.
**Participants evaluation** (baseline and post-intervention)	Digital guidelines, video, and printed material to record the participants' baseline and post-intervention assessment data.	Digital guidelines, video, printed material plus guidelines for carrying out evaluations about: location, professionals involved, and the necessary care for reliable measures.

^a^20-h online training (21) + teaching materials. ^b^20-h online training (21)+ teaching materials + structured messages throughout the implementation process.

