### New description

The randomization and allocation of health professionals into the two groups (CCT + APA vs. TDA) will be performed after all PHC professionals complete the online training. Through a randomly generated computer sequence, we will randomize each facility to one of the intervention arms with all eligible professionals within each facility randomized to the same intervention arm to avoid cross-contamination within the same facility. However, multiple facilities within the same city may be randomized to different groups. After randomization, they will be asked to implement BCP-VAMOS in their workplaces. The randomization and assignment of groups will be under the responsibility of a single researcher and will be blind to the others involved in the implementation strategies and data collection.

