### Outcomes evaluation

The evaluation of the BCP-VAMOS implementation process will be carried out based on RE-AIM (22) and CFIR (23). These frameworks enable to measure the quantitative and qualitative impact of an intervention on public health (26).

This study, despite focusing exclusively on the characteristics of the implementation, will describe the individual dimensions of RE-AIM (Reach = R and Effectiveness = E) to determine the impact of implementation and ongoing support on the program adaptation to the real world. The organizational dimensions (Adoption = A, Implementation = I, Maintenance = M) will be assessed to determine the factors involved in the implementation's success (see Table 2).

**Table 2 T2:** RE-AIM and CFIR information to evaluate the implementation of BCP-VAMOS, version 3.0. Brazil.

**RE-AIM, dimensions**	**RPT aims and outcomes measures**
^**a**^**Reach:** measure of participation in the intervention (individual level)	**Aim:** to describe the number, proportion, and representativeness of the participants in the intervention. **Quantitative:** recruitment, participation, and retention rates of participants calculated by PHC professional who will deliver the intervention. *Data collection:* registration of interested, enrolled, retained, and dropouts.
^**a**^**Effectiveness:** measure of the intervention's impact (individual level)	**Aim:** to show the results of the primary intervention outcomes. **Quantitative:** proportion of participants showing a behavior change in PA and EB by PHC professional. *Data collection:* baseline and post-intervention assessment.
**Adoption:** measure of the participation of location/teams interested in initiating the intervention (staff level)	**Aim:** to describe number, proportion, representativeness, and the characteristics of the location/PHC professionals who initiated the delivery of the intervention. **Quantitative:** adoption rate, demographic and social data of location/PHC professionals vs. the eligible ones. *Data collection:* electronic form filled out by PHC professionals. **Qualitative:** reasons that influenced the adoption and barriers to not adopt the intervention. *Data collection:* interview with PHC professionals.

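### The plan assigns the effect of the intervention to before-after tests, although both arms deliver BCP-VAMOS; the between-arm comparison should be named as the test of effect and adjusted for baseline

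*Protocol article*

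**What the plan says.** The abstract of the protocol article describes the randomised contrast as "comparing a group of PHC professionals who will participate in a traditional didactic approach (control group) vs. a group that will receive ongoing support". Under Description of the study design, both groups take the same 20-hour online training. Under New description, the facility is the randomised unit, and of the professionals in both arms it says: "After randomization, they will be asked to implement BCP-VAMOS in their workplaces". No arm goes without the programme.

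The Data analysis section then gives three rules:

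- Group characteristics: "To compare the characteristics between the groups, Fischer's exact and chi-square tests will be used".
- Effect: "To verify the effect of the intervention, Student's paired t test or Wilcoxon test (continuous variables) and McNemar test (categorical variables) will be used".
- Changes: "To compare changes between groups, Student's t test or Mann-Whitney *U*-test will be applied".

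The level is stated as "The analyses will be performed using a 5% probability", without saying whether it is one- or two-sided.

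Outcomes evaluation says that effectiveness will be judged by comparing the intervention group with the control group, at the level of the professional. Table 2 gives the quantitative effectiveness measure as "proportion of participants showing a behavior change in PA and EB by PHC professional".

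**The concern.** The sentence that carries the word effect points to tests that cannot see the randomised contrast. A paired t, Wilcoxon or McNemar test asks whether participants differ between baseline and 9 months. Where everyone is offered the programme, the answer combines the programme, any time trend and regression to the mean, whichever arm is examined.

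Regression to the mean is expected here, because low physical activity and inappropriate eating are among the reasons for enrolment and are also the primary outcomes. It is only partial, because the criteria are joined by and/or: a person may also enter through overweight or chronic disease.

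Two results could be misreported. A significant improvement in both arms could be presented as a proven effect. A significant improvement in one arm only could be presented as an effect of support. The plan names a between-arm test but does not say that it takes precedence.

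**Working it through.** **Inputs.** The article gives a minimum of 8 people per group and about 45 professionals: 8 × 45 = 360, which reproduces its own figure. This is a feasibility count; no effect size, SD or power is stated. My assumptions are 1:1 allocation (180 per arm), two-sided 5%, normally distributed outcomes in SD units, baseline-to-follow-up correlation r of 0.3 to 0.7, and independent participants. Clustering is ignored, so the figures show relative behaviour and are not a power statement for this trial.

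**1. Regression to the mean with no effect at all.** If the lowest share q of the population on the outcome is enrolled, with cut-point c, the expected change is (1 − r) × φ(c)/q.

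- q = 0.5, r = 0.5: 0.5 × 0.3989/0.5 = 0.40 SD.
- Over q of 0.3 to 0.7 and r of 0.5 to 0.7, the shift is 0.15 to 0.58 SD. A paired test in one arm is then significant with probability 0.77 to about 1.00.
- In 4,000 simulated trials with no effect in either arm (q = 0.5, r = 0.5), the paired test was significant in both arms in 100%. The t test on changes between arms rejected in 5.05%.

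These figures assume that everyone is selected on the outcome. Suppose instead that half are selected in this way and half sit at the population mean. For q = 0.5, r = 0.5 the shift is 0.5 × 0.40 = 0.20 SD. The SD of change is about 0.98, so the standard error is 0.98/√180 = 0.073 and the ratio is 2.73. The chance of a significant paired test is Φ(2.73 − 1.96) = 0.78. In the mildest case above (q = 0.7, r = 0.7) the same dilution gives a shift of 0.07 SD and a chance of 0.26. Dilution weakens the problem but does not remove it.

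**2. Equal true change in both arms.** If each paired test has power p, exactly one arm is significant with probability 2p(1 − p): 0.50 at p = 0.5 and 0.32 at p = 0.8. With 180 per arm, a common change of 0.15 SD and r = 0.5, p = 0.52 and the probability is 0.50. Over common changes of 0.10 to 0.20 SD and r of 0.3 to 0.7, it ranges from 0.12 to 0.50. The direct comparison has a 5% false-positive rate throughout.

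**3. Baseline as a covariate.** The variance of a change score is 2(1 − r), and that of a baseline-adjusted follow-up value is 1 − r². The ratio is (1 + r)/2.

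| r | Change score | Adjusted | Ratio |
|---|---|---|---|
| 0.3 | 1.40 | 0.91 | 0.65 |
| 0.5 | 1.00 | 0.75 | 0.75 |
| 0.7 | 0.60 | 0.51 | 0.85 |

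Unadjusted change scores therefore need 1/0.85 = 1.18 to 1/0.65 = 1.54 times as many participants for the same precision.

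**4. The binary outcome.** Set against Table 2, the Data analysis section names McNemar for categorical effect, Fisher and chi-square for group characteristics, and t or Mann-Whitney for changes. None is tied expressly to a comparison of proportions between arms.

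**The case against.** The strongest reply is that the randomised contrast is planned. The Data analysis section includes a between-group test of changes, and Outcomes evaluation repeatedly refers to comparing the two groups. The word intervention also often means the programme, so the paired tests may be meant as a before-after account of BCP-VAMOS. Nor does the article say whether they are run per arm or pooled. All of this stands, and it limits the point. It does not rescue the sentence, because on either reading a test without a comparator is given the task of verifying an effect.

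A reader might infer more than the article supports:

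- *That the arms will be compared only through their separate p-values.* No such rule is stated. The figures of 0.50 and 0.32 describe a misreading that the wording permits, not a planned decision rule.
- *That McNemar is the only route for the binary outcome.* A proportion calculated for each professional is a number and could enter the between-group t or Mann-Whitney test. The article does not say so, so the route is unclear and not absent.
- *That unadjusted change scores are biased by different recruitment and that baseline adjustment cures this.* Table 1 does give the supported arm "Printed material plus guidelines to optimize dissemination and recruitment: who, where, when, and how", but the control arm's training and materials also cover recruitment. With a baseline imbalance d, change scores are off by d(1 − r) if both arms regress to a common mean. If the arms come from populations with stable, different means, change scores are unbiased and the adjusted analysis is off by that amount: 0.3 × 0.5 = 0.15 SD at d = 0.3, r = 0.5. The article cannot settle which case applies.
- *That age, sex and BMI are available as covariates.* Participants' sex is not mentioned; age and overweight appear only as eligibility criteria.

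Covariate lists and the exact binary model may properly be left to an analysis plan that is not shown. The assignment of effect to paired tests is stated here and is wrong as stated.

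**Conclusion.** The concern holds in a limited form. The stated test of effect answers a before-after question, whereas the trial randomises ongoing support and promises a comparison of the two groups. Under regression to the mean alone, a paired test in one arm would be significant with probability 0.77 to about 1.00 if all participants are selected on the outcome. If half are, the two cases worked give 0.26 and 0.78. The between-arm test holds its 5% level under the independence assumed.

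The between-arm comparison is present but not designated as the test of effect, and its form for the binary measure is not clear. The lack of baseline adjustment is a lesser matter: it costs precision, with a variance ratio of 0.65 to 0.85, and is not shown to cause bias. The correlations, eligible shares, allocation ratio and independence of participants are assumptions; only the 360 comes from the article.

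**What to change.** Reword the Data analysis section as follows:

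- Define the effect as the difference between the supported and control arms at 9 months, with a 95% CI, from a model of the 9-month value on arm and the baseline value of the same outcome.
- State a corresponding between-arm analysis for the proportion showing behaviour change.
- Let both analyses respect the facility, which is the randomised unit.
- Report before-after changes descriptively, and do not use paired t, Wilcoxon or McNemar results as evidence of effect.
- Add further case-mix covariates only where they are collected, and do not present the adjustment as removing bias from differential recruitment.

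The baseline values of the primary outcomes are already to be collected, so the core change needs no new data. The cost is a change of wording and slightly more analysis work.

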### Randomization

The randomization and allocation of health professionals into the two groups (CCT + APA vs. TDA) will follow a sequence randomly generated by a computer. This process will be carried out after all the PHC professionals complete the online training. Health professionals from the same workplace will be assigned to the same group should more than one professional participate in the online training. After randomization, they will be asked to implement the BCP-VAMOS in their workplaces. Randomization and group assignment will be under the responsibility of one single researcher and will be blinded to the others involved in the implementation strategies and data collection.

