**Reach** is a measure at the individual level of participation, which refers to the characteristics and percentages of the target population's participation in the intervention (22). In this study, reach will be assessed as the number, proportion, and representativeness of program recipients enrolled and retained in the program. We will assess the involvement of program recipients based on three reach rates: recruitment (ratio between the number of users interested in participating in the program in relation to the number of exposed users—users served at the UBS during the period when the program was announced, multiplied by 100); participation (ratio between the number of participants who will start the program in relation to the number of eligible participants in the program, multiplied by 100); retention (ratio between the number of participants who will complete and the number of participants who started the program, multiplied by 100). These reach rates will be calculated by PHC professional, comparing the IG to the CG.

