**Effectiveness**, assessed at the individual level, refers to the extent of the intervention's impact on the primary outcomes, how it changes behavior and affects the quality of life, and whether or not there are unintended results (positive or negative) (22). In this study, effectiveness will be assessed considering the primary outcomes of BCP-VAMOS: physical activity and eating behavior. Physical activity will be assessed through a self-report of the weekly practice (type, frequency, and duration) (34) and by accelerometry (35), which allows measuring the time spent on sedentary behavior, light, moderate, and vigorous physical activity. Eating behavior will be assessed through the habit and frequency of consumption of foods classified as healthy (fruits, greens, and raw or cooked vegetables) and unhealthy (sweets, snacks, and sugary drinks) (34). These data will be collected by the PHC professionals through a validated questionnaire for the BMC-VAMOS program (33). The effectiveness outcomes will be analyzed by PHC professional (staff level) to assess the impact of intervention strategies, comparing the IG to the CG.

**Adoption** is a measure at the organizational level of participation that refers to the representativeness of locations and/or agents who are willing to implement an intervention, considering those who are eligible (22). In this study, the number, proportion, and representativeness of local/PHC professionals who initiate the program delivery will be calculated using those certified by the online training with eligibility criteria. We will calculated the adoption rate by considering the ratio between the number of PHC professionals who initiated the implementation of the program in each UBS and the number of PHC professionals certified by the online training, multiplied by 100. To identify the factors that will influence the program adoption and non-adoption, qualitative data will be collected through interviews with PHC professionals.

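### Facilities are randomised, but the named between-arm tests make no allowance for facility and their unit is not stated, so the 5% level is not protected

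*Protocol article*

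**What the plan says.** **Allocation.** The section headed New description states that "we will randomize each facility to one of the intervention arms with all eligible professionals within each facility randomized to the same intervention arm". The Randomization section before it speaks of allocating professionals, but has the same effect for shared workplaces: "Health professionals from the same workplace will be assigned to the same group should more than one professional participate in the online training". Both sections foresee facilities with more than one trained professional.

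**Unit of analysis.** Under Outcomes evaluation, the Effectiveness paragraph says "The effectiveness outcomes will be analyzed by PHC professional (staff level) to assess the impact of intervention strategies, comparing the IG to the CG". The Reach paragraph says "These reach rates will be calculated by PHC professional, comparing the IG to the CG". The Implementation paragraph has the same rule, and Table 2 defines effectiveness as a proportion of participants changing behaviour, per professional.

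**Tests.** Data analysis reads "To compare changes between groups, Student's t test or Mann-Whitney" U for change between arms, and "To compare the characteristics between the groups, Fischer's exact and chi-square tests will be used". For the effect of the intervention it lists paired t or Wilcoxon and McNemar. The level is given as "The analyses will be performed using a 5% probability", without sidedness. The section does not say which unit enters any test. No mixed model, GEE, facility summary or design effect is mentioned.

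**Size.** Study location and participants expects about 45 professionals with at least 8 people each, hence at least 360 adults. It does not give the expected number of facilities.

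**The concern.** The data have three levels: participants within a professional's group, professionals within a facility, and facilities, which are what is randomised. People in one group share a facilitator, and professionals in one facility share management, patients and setting, so their outcomes are likely to be positively correlated. A two-sample t or Mann-Whitney test on units below the facility treats them as independent. Its standard error is then too small and it rejects too often.

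This is a stated choice of test that does not match the stated design, so it is not a detail left to an analysis plan. It bears on the comparison of ongoing support with didactic training for physical activity and eating behaviour, which the Abstract calls primary outcomes and whose results are meant to inform national policy.

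**Working it through.** **Inputs from the article:** about 45 professionals; at least 8 participants per group; facility as randomised unit; 5% level. The article's own figure reproduces: 45 × 8 = 360. It is a recruitment expectation; there is no power calculation to check.

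**Inputs assumed, because the article gives none:** two-sided testing; ICC among participants in a facility of 0.02, 0.05 or 0.10; correlation ρ of 0.1 to 0.4 between summaries of professionals in the same facility; one, two or three professionals per facility.

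**Formulas.** With m units per facility and correlation r, DE = 1 + (m − 1)r. The true level of an unadjusted 5% test is 2 × [1 − Φ(1.96/√DE)].

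**(a) Tests on one summary per professional**

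| Professionals per facility | ρ | DE | True level |
|---|---|---|---|
| 1 | any | 1.0 | 5.0% |
| 2 | 0.1 | 1.1 | 6.2% |
| 2 | 0.2 | 1.2 | 7.4% |
| 2 | 0.3 | 1.3 | 8.6% |
| 2 | 0.4 | 1.4 | 9.8% |

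If only some facilities are shared, the effect shrinks. Suppose 10 of the 45 professionals share five facilities. The mean cluster size seen by a professional is (35 × 1² + 5 × 2²)/45 = 55/45 = 1.22. DE is then 1 + 0.22 × 0.2 = 1.04 or 1 + 0.22 × 0.4 = 1.09, and the true level about 5.5% or 6.0%.

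**(b) Tests on participants**

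| Participants per facility | ICC | DE | True level | Effective N of 360 |
|---|---|---|---|---|
| 8 | 0.02 | 1.14 | 6.6% | 316 |
| 8 | 0.05 | 1.35 | 9.2% | 267 |
| 8 | 0.10 | 1.70 | 13.3% | 212 |
| 16 | 0.02 | 1.30 | 8.6% | 277 |
| 16 | 0.05 | 1.75 | 13.8% | 206 |
| 16 | 0.10 | 2.50 | 21.5% | 144 |

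**(c) Simulation check.** This used 6,000 null trials per scenario, 45 professionals with 8 participants each, allocation by facility and t tests. With facility and professional each carrying 2.5% of the variance, the rejection rates were:

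| Facilities | Participants as unit | Professional means | Facility means |
|---|---|---|---|
| 45, one professional each | 9.1% | 5.1% | 5.1% |
| 22 with two, 1 with one | 12.1% | 7.0% | 5.3% |
| 15, three each | 13.4% | 8.0% | 5.0% |

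The same layouts were also run with variance shares of 1% and 5% each. Over all nine scenarios the t test on facility means stayed between 4.5% and 5.3%. The mixed model and GEE were not simulated.

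**The case against.** The strongest defence is the repeated statement that outcomes are analysed per professional. Read naturally, each professional contributes one figure and the arms are compared on about 45 figures. That absorbs all clustering within a professional's group and leaves no inflation where a facility has one professional. Shared facilities may also be few: the state has 1,824 primary care centres against about 45 expected professionals, and the Randomization section treats sharing as conditional.

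Much of this stands. A reader might infer that the 5% level is simply wrong; the article does not support that, because on this reading it holds whenever facilities and professionals coincide. The defence is incomplete for two reasons. A professional is still below the randomised unit in any shared facility, a case that both allocation sections provide for. And Data analysis never says that its tests use professional summaries. McNemar, listed in the same paragraph, needs individual yes/no pairs, so participant-level testing remains a possible reading.

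Other stronger inferences also fail:

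- **Confidence intervals are wrong.** None are planned; only a significance level is stated.
- **Every listed test is a faulty arm comparison.** Paired t, Wilcoxon and McNemar are before-after tests, and Fisher and chi-square are named for characteristics. Student's t or Mann-Whitney is what is stated for change between arms.
- **The t and Mann-Whitney tests must be deleted.** They are valid on one summary per facility.
- **A finding in favour of ongoing support could be facility variation alone.** That is too strong for a staff-level analysis with modest, conditional inflation.

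**Conclusion.** The concern holds in a limited form. The unit of allocation is the facility, the stated unit of analysis is the professional, and the section naming the tests neither states its unit nor allows for facility. The 5% level is therefore unprotected rather than demonstrably wrong.

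If tests use professional summaries, the true level runs from about 5% when no facility is shared to about 6% to 10% when every facility has exactly two professionals. The latter layout is an assumption that the article does not state, and partial sharing lies in between. The participant-level figures are a worst case that applies only if the tests are run on individuals. The mismatch of units can be read directly from the text, but its size cannot be settled from the article.

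**What to change.** In Data analysis, make the facility the unit for all between-arm outcome comparisons, in one of two ways:

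1. Reduce the data to one summary per facility and apply the t or Mann-Whitney test to those summaries, with degrees of freedom equal to facilities minus 2 for the t test (43 with 45 facilities, 21 with 23).
2. Fit a mixed model or GEE with facility as the cluster and a small-sample correction.

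These are alternatives and need not give identical results, so one should be named in advance. State the unit for every test. Align the per-professional wording under Outcomes evaluation, and the Randomization section, with allocation by facility as set out in New description.

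The cost is a change of wording. Facility membership must be known in order to randomise, so it should be available for analysis, although the article does not say that it is recorded in the dataset. The downside is somewhat larger p-values and less precision, more so if many facilities are shared.

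### Physical activity and eating behaviour are both called primary, but neither has a deciding variable in one stated form, and a single 5% level covers all analyses

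*Protocol article*

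**What the plan says.** The Abstract (Methods and analysis) says recipients are assessed at baseline and at 9 months "to measure markers of physical activity and eating behavior (primary outcomes"). Under Outcomes evaluation, the Effectiveness paragraph repeats this: "effectiveness will be assessed considering the primary outcomes of BCP-VAMOS: physical activity and eating behavior". It then lists how each domain is measured:

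- Physical activity by "self-report of the weekly practice (type, frequency, and duration").
- Physical activity also by accelerometry, "measuring the time spent on sedentary behavior, light, moderate, and vigorous physical activity".
- Eating behaviour by habit and frequency of eating foods classed as healthy ("fruits, greens, and raw or cooked vegetables) and unhealthy (sweets, snacks, and sugary drinks").

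The Effectiveness row of Table 2 describes the outcome differently: the share of participants who changed in each domain, calculated per professional. It gives no threshold for what counts as change.

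Data analysis compares changes between groups by Student's t test or Mann-Whitney and adds: "The analyses will be performed using a 5% probability". It names no lead measure, no order among measures and no rule for which result counts as success.

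**The concern.** A primary outcome should tell the reader, before any data are seen, which number answers the question. Here each domain is open in two ways.

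**Which measure.** Self-report and accelerometry can disagree, and neither takes precedence. Their risks of bias also differ. According to Data collection, the questionnaire data are gathered by the health professionals who deliver the program, and these are the people randomized. Accelerometry is gathered on site by a trained researcher.

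**Which form.** A change score per participant, a changed/not-changed classification and a proportion per professional are different variables. Table 2 points to the last two. The t or Mann-Whitney comparison could apply to change scores or to proportions per professional, and the text does not say which.

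If any of these results at 5% may carry the effectiveness claim, the chance of a false claim exceeds 5%, and a reader cannot tell by how much.

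**Working it through.** **The plan's own figure.** The article states no familywise error rate or power. Its only computed size is the expected number of adults under Study location and participants, 45 × 8 = 360. That reproduces but does not bear on this point.

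**Inputs**
- Level per test: 5% (Data analysis). Whether one- or two-sided is not stated; I assume two-sided.
- Number of measures, m: not stated. Possible readings are:
  - Only the Table 2 proportions, one per domain: m = 2.
  - One self-report score, four accelerometer classes, and healthy and unhealthy foods as two scores: 1 + 4 + 2 = 7.
  - As above, with the six listed foods kept separate: 1 + 4 + 6 = 11.
  - As above, with type, frequency and duration of self-reported activity also separate: 3 + 4 + 6 = 13.
- Correlation between measures, r: not given. I use 0 and assumed values of 0.3, 0.5 and 0.7.

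**Formula, independent tests:** P(at least one false positive) = 1 − 0.95^m.
- m = 2: 1 − 0.9025 = 9.75%
- m = 7: 1 − 0.6983 = 30.2%
- m = 11: 1 − 0.5688 = 43.1%
- m = 13: 1 − 0.5133 = 48.7%
- m = 14: 51.2%, the first count to pass one half

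**Correlated tests**, by simulation (400,000 draws of equally correlated two-sided z tests, each at 5%):

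| m | r = 0.3 | r = 0.5 | r = 0.7 |
|---|---|---|---|
| 2 | 9.5% | 9.1% | 8.3% |
| 11 | 37.7% | 30.3% | 22.3% |
| 13 | 41.8% | 33.5% | 24.0% |

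For two-sided tests on jointly normal statistics, correlation can only lower the rate (Šidák's inequality), so the independence figure is the ceiling for each m. Only between-group tests are counted. The paired tests that Data analysis also lists, and the three reach rates, are left out.

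**The case against.** Four points can be made in the plan's defence.

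**The count.** A reader might infer that about eleven primary endpoints are each tested. The document does not say so. It says what the instruments capture, and the foods can be read as illustrating two classes. Table 2 supports a reading with just two endpoints. This stands, so eleven can only be an assumed count.

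**The probability.** A reader might infer that a chance finding is likely. Even 43.1% is below even odds, and independence is a poor base case: the four accelerometer classes divide the same monitored time, and self-report measures the same behaviour. This stands too.

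**The implementation focus.** A reader might see a flat contradiction between primary behavioural outcomes and "This study, despite focusing exclusively on the characteristics of the implementation". The rest of that sentence explains that reach and effectiveness are included to show the impact of implementation and support. The Effectiveness paragraph calls the two behaviours the program's primary outcomes. The passages can be read together. What remains is that the Abstract gives the label while describing this trial, so their status needs one clear statement.

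**Unseen documents.** Multiplicity method and item scoring commonly sit in the full protocol or analysis plan, and the registry entry is not at hand. A reader might infer that the deciding measure will be picked after the results are known; the article cannot establish that. But the point does not rest on a missing method. The article itself names two primaries, describes them in forms it does not reconcile, and puts them all under one 5% level.

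**Conclusion.** The point holds as a defect in how the primary outcomes are fixed. Even on the reading kindest to the plan, two co-equal outcomes at 5% each give up to 9.75%, nearly double the stated level. If eleven measures were each tested, the rate would be at most 43%, and about 38%, 30% or 22% at correlations of 0.3, 0.5 or 0.7. The true figure depends on a count that the article leaves anywhere from 2 to 13.

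These rates assume two-sided tests that each hold their nominal 5%, no true effect on any measure, and a claim that any one significant result would support. The correlations are assumptions. The case for change is moderate: the defect affects how the effectiveness result can be read, and it can be corrected with data already planned.

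**What to change.** 1. Name one physical activity variable. Accelerometer minutes of moderate-to-vigorous activity is one example: the delivering professionals do not collect it, and participant screening already refers to weekly minutes at that intensity.
2. Name one eating variable from the existing questionnaire.
3. Give each variable in one form (change score or proportion changed, with the cut-off if the latter), and make Table 2 and Data analysis agree with it.
4. Test the two with Holm at 5% overall: the smaller p-value against 0.025 and, if that is met, the larger against 0.05.
5. Label all other behavioural measures supportive and report them with confidence intervals.
6. State whether these are the trial's primary outcomes or only the program's, so that the Abstract agrees with Outcomes evaluation. If only the program's, name the trial's own primary outcome.

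**Cost.** A few lines in the protocol, plus a registry entry, which Study design already promises for any change. The smaller p-value must meet 0.025 instead of 0.05, which costs some power. An accelerometer primary depends on complete on-site collection; if that is in doubt, another single variable can be named. Whether the questionnaire already yields a single eating score cannot be checked from the article.
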